## Abstract

**Background:**

Older Americans, a growing segment of the population, have an increasing need for surgical services, and they experience a disproportionate burden of postoperative complications compared to their younger counterparts. A preoperative comprehensive geriatric assessment (pCGA) is recommended to reduce risk and improve surgical care delivery for this population, which has been identified as vulnerable. The pCGA optimizes multiple chronic conditions and factors commonly overlooked in routine preoperative planning, including physical function, polypharmacy, nutrition, cognition, mental health, and social and environmental support. The pCGA has been shown to decrease postoperative morbidity, mortality, and length of stay in a variety of surgical specialties. Although national guidelines recommend the use of the pCGA, a paucity of strategic guidance for implementation limits its uptake to a few academic medical centers. By applying implementation science and human factors engineering methods, this study will provide the necessary evidence to optimize the implementation of the pCGA in a variety of health care settings.

**Objective:**

The purpose of this paper is to describe the study protocol to design an adaptable, user-centered pCGA implementation package for use among older adults before major abdominal surgery.

**Methods:**

This protocol uses systems engineering methods to develop, tailor, and pilot-test a user-centered pCGA implementation package, which can be adapted to community-based hospitals in preparation for a multisite implementation trial. The protocol is based upon the National Institutes of Health Stage Model for Behavioral Intervention Development and aligns with the goal to develop behavioral interventions with an eye to real-world implementation. In phase 1, we will use observation and interviews to map the pCGA process and identify system-based barriers and facilitators to its use among older adults undergoing major abdominal surgery. In phase 2, we will apply user-centered design methods, engaging health care providers, patients, and caregivers to co-design a pCGA implementation package. This package will be applicable to a diverse population of older patients undergoing major abdominal surgery at a large academic hospital and an affiliate community site. In phase 3, we will pilot-test and refine the pCGA implementation package in preparation for a future randomized controlled implementation-effectiveness trial. We anticipate that this study will take approximately 60 months (April 2023-March 2028).

**Results:**

This study protocol will generate (1) a detailed process map of the pCGA; (2) an adaptable, user-centered pCGA implementation package ready for feasibility testing in a pilot trial; and (3) preliminary pilot data on the implementation and effectiveness of the package. We anticipate that these data will serve as the basis for future multisite hybrid implementation-effectiveness clinical trials of the pCGA in older adults undergoing major abdominal surgery.

**Conclusions:**

The expected results of this study will contribute to improving perioperative care processes for older adults before major abdominal surgery.

**International Registered Report Identifier (IRRID):**

DERR1-10.2196/59428

## Introduction

### Background

Each year, approximately 4.5 million older adults undergo major surgery [1]. On average, 25% of these older adults develop postoperative complications, costing the health care system approximately US $8000 to US $13,000 per complication [2] and an average of US $20,000 to US $30,000 for the postoperative hospitalization [3-6]. Unfortunately, the risk of complications doubles with preoperative functional decline, frailty, or cognitive impairment [7-14], which are risk factors that are rarely measured. A preoperative comprehensive geriatric assessment (pCGA) is a multicomponent intervention evaluating and optimizing multiple chronic conditions and factors commonly overlooked in routine preoperative planning, including physical function, polypharmacy, nutrition, cognition, mental health, and social and environmental support [15]. Major abdominal surgery carries unique risks, disrupting the core muscles with often-delayed functional recovery [16-21], cognitive decline [17,20,22-24], and disproportionately high morbidity and mortality [7,25-28]. When implemented properly, the pCGA improves outcomes for patients undergoing abdominal surgery, reducing postoperative complications by 40% and length of stay by 2 days [29,30].

Experts and best practice guidelines recommend a pCGA for all older patients undergoing major surgery [15,31-33]. In prior work with the American College of Surgeons, an expert consensus conference of >50 stakeholder organizations generated national standards for the surgical care of older adults through the Geriatric Surgery Verification Program [34,35]. These standards include conducting a pCGA for older surgical patients. Defining the standards is a critical first step; however, this work is incomplete without generalizable implementation strategies applicable to real-world settings. A lack of evidence on how best to implement the pCGA in a variety of health systems has limited patient access to this intervention [36]. The few implementation studies that exist demonstrate challenges due to contextual factors (eg, misaligned incentives) and low fidelity to the intervention [36,37]. As a result, few programs use the pCGA for older surgical patients, and reach is limited to patients receiving care at large academic medical centers with significant resources. Thus, there is a critical need for novel, evidence-based strategies to promote the successful implementation of this intervention in a variety of health care settings. To address this gap, this study seeks to answer the research question “What implementation strategies will improve provider use (adoption) and patient access (reach) to the pCGA, while preserving effectiveness (fidelity) in academic and community medical settings?”

### Objectives

The overall objective of this study is to use implementation science and systems engineering methods to tailor and pilot-test a user-centered pCGA implementation package that can be adapted to community-based hospitals for future multisite implementation-effectiveness trials. Therefore, we aim to (1) map the pCGA process and identify system-based barriers and facilitators to its use among older adults undergoing major abdominal surgery, (2) co-design a pCGA implementation package applicable to a diverse population of older patients undergoing major abdominal surgery at a large academic hospital and an affiliate community site, and (3) test and refine the pCGA implementation package in preparation for a future randomized controlled implementation-effectiveness trial. We hypothesize that systems engineering methods of process mapping and co-design can successfully be applied to the pCGA (aims 1 and 2) and that a rigorous user-centered pCGA implementation package will improve surgical care processes (reach and adoption, which are the primary implementation outcomes) and patient outcomes (length of stay, which is the primary effectiveness outcome) for older adults undergoing major abdominal surgery.

## Methods

### Design and Conceptual Framework

This study will apply implementation science and human factors engineering principles to optimize the delivery of an existing, effective intervention—the pCGA—and generate an adaptable implementation package for future work. Through process mapping, supplemented with observation and interviews, we will identify opportunities for system redesign that will improve pCGA delivery (phase 1) and use participatory design with patients, caregivers, and health care providers to develop a user-centered implementation package (phase 2) that is adaptable to academic and community settings. Subsequently, we will pilot-test the implementation package (phase 3) using the reach, effectiveness, adoption, implementation, and maintenance (RE-AIM) framework [38], generating preliminary data in preparation for a larger randomized controlled implementation-effectiveness trial. This work aligns with the National Institutes of Health (NIH) Stage Model [39] for intervention development, considering implementation early in development (stage IA) and recognizing that the development and evaluation of complex interventions may not be linear.

The pCGA (Table 1) is based on a model by McDonald et al [29] that has demonstrated decreased length of stay, readmission rates, and discharge to nonhome destination for patients undergoing abdominal surgery. To improve outcomes, the pCGA must be implemented with fidelity to key elements [15]. Treatment fidelity, particularly for complex behavioral interventions, is conceptualized as consistency in the content of the intervention, the quality of intervention delivery by health care professionals, and the receipt and adherence by patients [40]. The content of the pCGA requires a multidomain assessment [41,42]; however, equally important are the presence and quality of a follow-up plan to optimize identified deficits, as well as patient adherence to this plan. The pCGA often generates recommended tasks for the patient (exercises and nutritional shakes) and provider (medication changes) or identifies additional preoperative workup to be performed (imaging or physiological testing). Many studies on pCGA fall short by using it primarily as a risk stratification tool without a plan or sufficient time to address modifiable factors [43-45]. In addition to the aforementioned study by McDonald et al [29], studies from the United Kingdom have demonstrated that the pCGA, performed in multidisciplinary settings with a plan to address deficits, reduces postoperative length of stay and complications [30,46]. These studies have led to national and international guidelines that recommend a pCGA for older adults before major surgery [15,31-33].

Systems engineering methods improve health care delivery and outcomes by tailoring the fit of the intervention to the local context. A seminal report from the Institute of Medicine and the National Academy of Engineering outlines the unique methods and tools by which systems engineering can transform the quality and delivery of health care [47]. We will use a human factors engineering model: the systems engineering initiative for patient safety (SEIPS) model [48]. It builds on the structure-process-outcome model developed by Donabedian [49] by providing a detailed and expanded structure of the interacting components (ie, the work system)—people (or teams), tasks, tools and technology, organizational factors (eg, policies and teamwork), physical environment (clinic location), and external environment—that influence health care processes and outcomes. SEIPS has been extensively and successfully applied to health care delivery [50-58], including work to improve care transitions for older adults [59-64]. We will use SEIPS 2.0 [65], which expanded the original model [48] to acknowledge that patients and families perform work within the health care process and that their internal environment (ie, patient home) plays a role within the system (Figure 1).

**Table 1 table1:** Preoperative comprehensive geriatric assessment.

Domain	Assessment	Staff performing the assessment	Example output
Polypharmacy	Medication reconciliation Identification of high-risk Beers criteria medications Anticholinergic cognitive burden score	Pharmacist	Medication changes made directly or referred to PCP^a^
Medical comorbidities	History and physical examination, including cardiac risk assessment with revised cardiac risk index	Geriatrician	Additional testing ordered; specialist referral placed
Physical function	Mobility testing (eg, Timed Up and Go Test) Lawton Independent Activities of Daily Living scale, activities of daily living, and home support and resources	Medical assistant and social worker	Home exercises prescribed or preoperative physical therapy referral (“prehabilitation”)
Cognition	Delirium risk assessment (eg, Montreal Cognitive Assessment)	Social worker	Memory clinic referral
Mood	Depression screen (eg, Patient Health Questionnaire-9)	Medical assistant	Medication or specialist referral
Nutrition	Nutritional status (eg, Mini Nutritional Assessment–Short Form) and BMI	Medical assistant	Nutritional supplementation
Goals of care	Discussion and documentation of acceptable outcomes and code status Assist patient with documenting health care power of attorney	Geriatrician	DNR^b^ status established and communicated to surgeon

^a^PCP: primary care provider.

^b^DNR: do-not-resuscitate.

**Figure 1 figure1:**
[figure not shown]
Preliminary systems engineering initiative for patient safety model 2.0 depicting the preoperative comprehensive geriatric assessment process. CVA: cerebrovascular accident; VTE: venous thromboembolism.

The study was registered at ClinicalTrials.gov in accordance with NIH policies and regulations (phases 1 and 2 [observational phases]: NCT06184919; phase 3 [pilot trial]: NCT06184724).

### Ethical Considerations

The study will be conducted in 3 phases. Each phase will be reviewed separately by the institutional review board (IRB) of the University of Wisconsin–Madison. Phase 1 of the study was approved by the IRB on January 19, 2023 (2022-1516). All participants provide informed consent for both observations and interviews. To protect privacy and confidentiality, all data are deidentified. Compensation is provided in the form of gift cards. Participants receive US $20 for participating in observations and US $20 for a 45-minute qualitative interview. Health care staff receive US $45 for a 90-minute focus group. Surgeons receive US $50 for a 45-minute interview. Phase 2 of the study was approved by the IRB on March 1, 2024 (2024-0044). All participants provide informed consent. To protect privacy and confidentiality, all data are deidentified. Compensation is provided in the form of gift cards. Patient and caregiver participants receive US $50 per 90-minute session. Health care professionals receive US $100 per 90-minute session. Phase 3 study activities will be initiated after receiving approval from the IRB. All participants will be required to provide informed consent. To protect privacy and confidentiality, all data will be deidentified. Compensation will be provided in the form of gift cards. Participants will receive US $5 per completed survey.

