### Phase 3: Pilot Trial of the pCGA Implementation Package

#### Study Design

We will conduct a pretest-posttest pilot study of the implementation package over 10 months, conducted at the clinic level at 2 busy academic medical center surgical subspecialty clinics performing major abdominal surgery (selecting one that does not routinely refer for pCGA in addition to one that does routinely refer). We will collect baseline prepilot data via retrospective chart abstraction from the year before the intervention. After an implementation rollout period of 2 months, postintervention data will be collected over 10 months. Specifically, we will assess outcomes according to the RE-AIM framework [38], using chart abstraction for patient-level data and simple self-reported surveys for the health care professionals. We hypothesize that a user-designed implementation package will improve the reach and adoption of the pCGA compared to the historic baseline.

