##### Recruitment and Enrollment

Clinic staff will approach potential participants to determine interest, and a study team member will then share study details and obtain consent. At baseline, 40 patients per year are seen for pCGA. We expect to enroll 20 patients over the pilot period. All patient data for the pilot will be obtained via chart abstraction. The study will be subject to IRB approval.

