#### Outcomes

The primary outcomes of this pilot trial will be reach and adoption, assessed using the RE-AIM framework [38] (Table 2). Reach refers to the percentage and characteristics of older adults receiving the pCGA intervention, while adoption accounts for those health systems and health care professionals who refer patients for, or deliver, the pCGA [38,92]. Of note, implementation in the RE-AIM framework refers to fidelity, or the extent to which an intervention is delivered as intended. We will expand the implementation domain to include measures of fidelity, as defined by NIH Best Practices [40], as well as feasibility, acceptability, and appropriateness according to the taxonomy of implementation outcomes developed by Proctor et al [93]. The primary effectiveness outcome will be postoperative length of stay, which is an easily measured, continuous outcome variable commonly used in the surgical literature on pCGA [29]. We will collect exploratory measures to inform the selection of effectiveness outcomes for a future implementation-effectiveness trial. These exploratory outcome measures will include (1) a composite of death or postoperative complication events; and (2) data points relevant to the pCGA, including a cognitive outcome (postoperative delirium), functional outcome (discharge destination to home, rehabilitation, or skilled nursing), nutritional outcome (discharge diet, albumin level, and weight at discharge), and polypharmacy (Beers criteria discharge medications [79], anticholinergic burden score [78], and number of opioid pain pills prescribed at discharge).

**Table 2 table2:** The reach, effectiveness, adoption, implementation, and maintenance (RE-AIM) domains and associated outcome measures.

Domain	Definition	Measurement
Reach	The percentage and characteristics of older patients who receive pCGA^a^ before abdominal surgery	Referred ÷ potentially eligible patients Comparison of referred ÷ eligible patients by age, sex, race, ethnicity, BMI, and zip code Target reach: >50% referral of eligible pCGA patients per clinic
Effectiveness	The improvement in clinical outcomes from pCGA receipt	Primary: postoperative length of stay Secondary: 30-day morbidity and mortality (refer to Chart Abstraction section)
Adoption	Surgeon intent, decision, and action to refer eligible patients for pCGA	Percentage of surgeons referring ÷ total surgeons in the pilot clinic Target adoption: >75% of surgeons achieving >50% referrals

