The pilot trial will test the pCGA implementation package using a pretest-posttest design at 2 surgical clinics enrolling 20 patients in the preimplementation period and 40 in the postimplementation period. Using the RE-AIM framework [38] we will measure reach, effectiveness, adoption, implementation, and maintenance. We aim to improve reach and maintain fidelity. Exploratory analyses will assess differences across traditionally underrepresented groups [69] (rural vs urban, racial majority vs minority groups, men vs women vs other gender identities, and Hispanic vs non-Hispanic ethnicity). We hypothesize that reach will increase while maintaining fidelity in the postimplementation phase of the pilot.

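### Phase 3 compares consented post-implementation patients with a retrospective chart baseline, leaving length of stay and the event estimates open to selection bias of unknown size and direction

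*Protocol article*

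**What the plan says.** Four places in the protocol article bear on who contributes patient outcome data in phase 3.

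- **Ethical Considerations:** "Phase 3 study activities will be initiated after receiving approval from the IRB. All participants will be required to provide informed consent". No exception or waiver is mentioned for any group.
- **Phase 3, Recruitment and Enrollment:** "Clinic staff will approach potential participants to determine interest, and a study team member will then share study details and obtain consent". The same paragraph says that all patient data for the pilot come from chart abstraction.
- **Phase 3, Study Design:** "We will collect baseline prepilot data via retrospective chart abstraction from the year before the intervention".
- **Results, Phase 3:** the pilot is described as "enrolling 20 patients in the preimplementation period and 40 in the postimplementation period".

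The Outcomes section makes reach and adoption primary for the pilot and postoperative length of stay the primary effectiveness outcome. It lists "a composite of death or postoperative complication events" among the exploratory measures, while Table 2 shows 30-day morbidity and mortality as secondary. The Objectives hypothesize that length of stay will improve. Data Analysis plans chi-square, t or Mann-Whitney tests at P<.05, and event rates with confidence intervals for planning a later study.

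**The concern.** The implementation package acts at clinic level, and surveys go only to health care professionals. As described, patient consent therefore has one visible effect on the data: it decides whose chart is counted. Only the post-implementation period clearly has that filter.

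If willingness or ability to consent is related to prognosis, the two periods would differ in length of stay and event rates even if the package did nothing. Such a link is plausible here. Eligibility includes cognitive and functional impairment, and the Introduction cites functional decline, frailty and cognitive impairment as raising complication risk.

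At stake are the primary effectiveness comparison and the event rates carried into the design of the next trial. The counts behind reach and adoption are a separate matter and are not part of this point.

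**Working it through.** **Step 1. Entry rule by period.** The plan has no sample-size or power figure to reproduce; Data Analysis says power calculations do not apply. The check starts from the text.

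| | Baseline year | Post-implementation |
|---|---|---|
| Entry | Retrospective charts (Study Design) | Approach, then consent (Recruitment and Enrollment) |
| Outcome source | Chart | Chart |
| Consent rule | None specific to this period; called enrolled in Results, Phase 3 | Consent required |

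The outcome source is the same in both periods. The entry rule is not. Read literally, the all-participants consent rule and the word for enrollment in Results would also cover the baseline, which fits poorly with retrospective abstraction. The article does not resolve this.

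**Step 2. How large could the effect be?** This is an illustration only. It assumes that the baseline holds all eligible operated patients, that case mix is the same in both periods, and that there is no true effect.

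Inputs:
- overall complication risk p = 0.25 (Introduction; an average over older adults having major surgery, used as an anchor)
- consent fraction c = 0.5 to 0.9 (assumed)
- risk ratio RR of decliners to consenters = 1.0 to 2.0 (assumed)
- extra stay d of decliners = 0 to 3 days (assumed)

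*Complications.* The overall risk is p = c·p_c + (1−c)·RR·p_c, where p_c is the risk in consenters. Hence p_c = p / [c + (1−c)·RR], and the spurious fall is p − p_c. For c = 0.5 and RR = 2: 0.25 / 1.5 = 0.167, a fall of 8.3 points.

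| c | RR 1.0 | RR 1.25 | RR 1.5 | RR 2.0 |
|---|---|---|---|---|
| 0.9 | 0 | 0.6 | 1.2 | 2.3 |
| 0.8 | 0 | 1.2 | 2.3 | 4.2 |
| 0.6 | 0 | 2.3 | 4.2 | 7.1 |
| 0.5 | 0 | 2.8 | 5.0 | 8.3 |

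(spurious fall, percentage points)

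If decliners are healthier the sign reverses. For c = 0.5 and RR = 0.5: 0.25 / 0.75 = 0.333, an apparent rise of 8.3 points.

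*Length of stay.* If consenters average m days, the overall mean is m + (1−c)·d, so the spurious fall is (1−c)·d.

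| c | d = 0 | d = 1 | d = 2 | d = 3 |
|---|---|---|---|---|
| 0.9 | 0 | 0.1 | 0.2 | 0.3 |
| 0.8 | 0 | 0.2 | 0.4 | 0.6 |
| 0.6 | 0 | 0.4 | 0.8 | 1.2 |
| 0.5 | 0 | 0.5 | 1.0 | 1.5 |

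(days)

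For scale, the Introduction credits the pCGA with a 2-day shorter stay.

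**Step 3. Against sampling error.** With 20 baseline and 40 post-implementation patients, the 95% half-width for a difference at a 25% rate is 1.96·√[0.25·0.75·(1/20 + 1/40)] = 0.232, about 23 points. For length of stay, assumed SDs of 3, 5 and 7 days give half-widths of 1.96·SD·√(1/20 + 1/40) = 1.6, 2.7 and 3.8 days. Sampling error is larger than most of the illustrated shifts.

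**The case against.** **The stakes are limited.** Reach and adoption are the pilot's primary outcomes. Data Analysis already warns that numbers are too small to judge mortality or morbidity, and the confidence intervals are wide. This stands and limits how serious the point is. The warning concerns sample size only, though. A selection difference does not shrink with more patients, and a confidence interval does not show it. Length of stay also carries a stated hypothesis of improvement.

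**A condensed article may leave consent detail to the full protocol.** This is fair for the wording of a waiver. The article does, however, itself state two entry routes for the groups it compares.

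**The quoted consent rule shows no asymmetry by itself.** Correct. The adjacent payment per survey fits professionals, the only group surveyed. Recruitment and Enrollment and the phase 3 Study Design carry the point.

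A reader might also draw stronger conclusions that the documents do not support:

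- *That the comparison is biased, or biased in the package's favor.* There is no consent rate and no consenter-decliner contrast, and the sign can go either way.
- *That deaths and complications are ascertained differently.* Both periods use charts. What differs is who is included.
- *That baseline deaths are lost because the dead cannot consent.* This needs past patients to be recontacted for consent, which no section describes.
- *That the baseline surely holds all comers.* No section says so. "At baseline, 40 patients per year are seen for pCGA" leaves open that baseline charts are themselves a selected set.
- *That decliners carry double risk.* The cited doubling contrasts patients with and without certain risk factors, and phase 3 eligibility already selects for such factors. A ratio of 2.0 is only the upper end of an assumed range.

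**Conclusion.** The point holds as a risk of selection bias. The plan selects post-implementation patients by consent and baseline patients from retrospective charts, then compares their length of stay and clinical events. Data Analysis and Limitations do not acknowledge this.

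Neither size nor direction can be read from the article. The illustrated ranges, 0 to 8.3 points on a 25% complication rate and 0 to 1.5 days of stay, rest on assumed consent fractions and assumed differences in decliners, and on a baseline of all eligible patients. They show that the effect could be anything from negligible to a sizable part of the cited 2-day benefit.

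The main target is length of stay. Complications and death are exploratory or secondary, and matter here mainly as planning estimates. A correction before phase 3 opens is worthwhile.

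**What to change.** - Use one selection rule for patient outcomes in both periods, and state the consent or waiver rule for each.
- Preferably, request a waiver of consent for deidentified chart abstraction in the phase 3 IRB review. The article describes that approval as still to come; it does not show whether a submission has been made.
- Compute length of stay, complications, death and discharge outcomes on all eligible operated patients of the two clinics in each period. Keep consent for the health professional surveys.
- If the waiver is refused, report the patient outcomes descriptively for consenters, drop the before-after significance tests on them, and add the selection difference to Limitations.
- While revising, reconcile the counts: Recruitment and Enrollment expects 20 patients over the pilot, while Results, Phase 3 gives 20 before and 40 after.

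The cost is the waiver request and the abstraction of some more charts; all pilot patient data already come from charts. The downside is that the waiver may be refused, which leaves the descriptive option. With one rule in both periods, the consent-related difference is removed by design.
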